## Methods

### Study Setting

The trial will be conducted at Amrita School of Dentistry, AIMS, Kochi and Amrita Urban Health Centre, Kaloor, Kochi, Kerala, India.

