### Recruitment

The adults visiting for routine dental care prosthodontics, Amrita School of Dentistry or at Amrita Urban Dental Health Centre will be recruited for the study. On examination, if the patient is found to satisfy the inclusion criteria, then they will be given options for the management of TMD by prosthetic rehabilitation or by splints. If the patient opts for prosthetic rehabilitation, then an option of participation in the trial will be explained, and the consenting process is followed. In case the patient declines to participate in the trial, the missing teeth will be managed according to the standard protocol of the department.

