### Sequence Generation

The selected patient for trial will be randomly allocated to either the intervention arm or the control arm of their group, as per computer-generated randomization, schedule stratified, based on the type of group it belongs. The selected individuals will be allocated in equal probabilities to the intervention and control groups by stratified randomization. Stratified randomization is achieved by performing a separate randomization procedure within each of the two strata of participants. This will ensure that the numbers of participants receiving each intervention are closely balanced within each stratum. Treatment assignments are then made from separate randomization lists created in advance of the trial for each stratum.

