### Allocation Concealment Mechanism

Allocation concealment will be ensured, the randomization code will not be released until the patient has been recruited into the trial, which takes place after all baseline measurements have been completed. The randomized codes, kept in a sealed cover at each clinic, will assign the patient to the intervention at baseline visit. The statistician will design the randomization schedule.

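### Two clinics recruit, but neither the stratification nor the stated pain comparisons use clinic: a small, avoidable loss of precision, not a bias

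*Protocol article*

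**What the plan says.** Study Setting names two sites, a dental school and an urban health centre: the trial is "conducted at Amrita School of Dentistry, AIMS, Kochi and Amrita Urban Health Centre". Recruitment confirms that both enrol, since adults attending "Amrita School of Dentistry or at Amrita Urban Dental Health Centre will be recruited for the study".

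Sequence Generation describes 1:1 allocation from a computer-generated "schedule stratified, based on the type of group it belongs". The groups are the three edentulism types. Allocation uses "separate randomization lists created in advance of the trial for each stratum". The same section speaks of "performing a separate randomization procedure within each of the two strata of participants", which does not match three groups. Clinic is not named as a factor.

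Allocation Concealment Mechanism places the codes at the sites: they are "kept in a sealed cover at each clinic". Implementation adds that the list itself stays with the doctoral committee.

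Statistical Methods and Table 3 give analysis of variance or chi-square methods for the main pain rows, applied to each person's reduction in VAS and GCPS. The subgroup rows use chi-square methods, apart from one regression row with an interaction term for groups 1 to 3. No row names clinic.

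**The concern.** Clinic is known before allocation, costs nothing to record, and could plausibly relate to how much pain falls. With strata defined by edentulism group alone, the text does not ensure that each arm has the same clinic mix within a 50 v 50 comparison. With no clinic term in the stated comparisons, any clinic difference in pain reduction is counted as unexplained variation. A chance imbalance would then move the treatment estimate without correction. What is at stake is the precision of the intervention-versus-control comparison within each edentulism group.

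**Working it through.** **Inputs from the document.** 50 per arm within each edentulism group; 1:1 allocation; power 80%, alpha .05 and effect size 0.77 (Sample Size).

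**Inputs assumed.** The document gives no clinic split and no clinic effect. I take splits of 50:50 and 70:30, and a clinic difference *d* in pain reduction of 0.2, 0.5 or 0.8 within-clinic SD. The 0.77 is stated for masticatory muscle activity on EMG, so using it for pain is also an assumption; an effect of 0.5 SD is shown beside it.

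**The plan's own figure.** The stated minimum is 22 per group. With n = 2(z_alpha + z_beta)²/0.77²:
- One-sided: 2(1.645 + 0.842)²/0.593 = 20.9, so 21; the t-test version gives 21.6, so 22.
- Two-sided: 2(1.960 + 0.842)²/0.593 = 26.5, so 27; the t-test version gives 28.

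The 22 thus reproduces as a one-sided calculation. The results below use two-sided tests at the planned 50 per arm.

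**Variance left in the error.** For clinic share *s*, the added variance is v = s(1 − s)d² relative to a within-clinic variance of 1. Its share of the total is v/(1 + v), and the SE grows by √(1 + v). Power at 0.77 is Φ(0.77/(√(1 + v)·√(2/50)) − 1.96). With v = 0 this is Φ(3.85 − 1.96) = 97.1%.

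| d | split | v | share of variance | SE factor | power at 0.77 |
|---|---|---|---|---|---|
| 0.2 | 50:50 | 0.010 | 1.0% | 1.005 | 96.9% |
| 0.5 | 50:50 | 0.0625 | 5.9% | 1.031 | 96.2% |
| 0.5 | 70:30 | 0.0525 | 5.0% | 1.026 | 96.4% |
| 0.8 | 50:50 | 0.160 | 13.8% | 1.077 | 94.7% |
| 0.8 | 70:30 | 0.134 | 11.8% | 1.065 | 95.1% |

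For *d* of 0.5 to 0.8 the loss from 97.1% is therefore about 1 to 2 points.

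**Simulation.** 50 per arm, 50:50 clinics, 10,000 runs per setting (Monte Carlo SE of power about 0.5 points), true effect 0.5 SD:

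| d | allocation | type I error without clinic | power without clinic | power with clinic |
|---|---|---|---|---|
| 0.5 | ignores clinic | 5.0% | 65.8% | 68.2% |
| 0.8 | ignores clinic | 5.0% | 63.7% | 69.6% |
| 0.5 | balanced by clinic | 4.4% | 67.2% | 69.4% |
| 0.8 | balanced by clinic | 3.3% | 64.2% | 69.7% |

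The gain from adjusting is about 2 to 6 points whether or not allocation happened to be balanced by clinic. If it was balanced, leaving clinic out makes the test conservative.

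**The case against.** **Covariates are commonly left to an analysis plan that is not shown.** Nothing in Table 3 excludes a clinic term, and an article may omit how lists are divided between sites. This stands in part: the analysis request may amount to a confirmation. The stratification factor, however, is set in this document, and so are the comparisons as stated.

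**The effect is small.** This stands. The outcome is each person's reduction in pain, so a constant clinic difference in pain level drops out, and only a difference in change matters. A clinic difference of 0.8 SD would exceed the design effect itself. Both sites are in Kochi and draw routine dental patients, and Data Collection Methods describes central training.

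**Stratifying by edentulism type alone is a legitimate design.** Agreed. A second factor is an improvement, not the repair of an invalid scheme.

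A reader might infer four stronger things:
- *Both clinics hold copies of one list, so codes opened at one reveal those still sealed at the other.* No text says this. Pre-assigned covers can validly be divided between sites, and the list stays with the doctoral committee.
- *Patients and treating dentists differ by clinic.* The document reports no such difference.
- *Arms will differ widely in clinic mix.* If allocation ignores clinic, the 95% range at 50 v 50 is 1.96·√(2s(1 − s)/50), about ±16 points at 80:20 and ±20 at 50:50. That needs an assumed split and an assumed mechanism. If blocks of four, say, were handed out whole, a clinic could be at most 2 patients out of balance, or 2/50 = 4 points. The text does not settle which applies.
- *The two strata are the two clinics.* The preceding sentences name group type as the factor, so the number needs clarifying. Were it true, clinic would belong in the model all the more.

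**Conclusion.** The point holds as a modest matter of design and precision. Two clinics recruit and hold codes, stratification is by edentulism group only, and the stated pain comparisons have no clinic term. Balance on clinic is therefore not guaranteed, and any clinic difference in pain reduction stays in the error.

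There is no systematic bias and no inflation of type I error. The loss is about 1 to 2 points of power at an effect of 0.77 and about 2 to 6 points at 0.5 SD, for 50 per arm. These sizes rest on assumed clinic differences of 0.5 to 0.8 SD that add to the outcome equally in both arms, and on an assumed split. At 0.2 SD the loss is negligible. The documents do not support a charge of broken concealment or of known differences between the clinics.

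**What to change.** 1. Include clinic, together with edentulism group, as a factor in the intervention-versus-control model for pain reduction, for all patients including those already randomised.
2. State in Sequence Generation and Allocation Concealment Mechanism that each clinic uses its own list per edentulism group (3 groups × 2 clinics = 6 lists), and correct the number of strata. If this is already the practice, only the text changes. If not, apply it to remaining patients only and keep all existing allocations.

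The first step costs one degree of freedom and is the main gain. The second is secondary because recruitment began in May 2021. It may leave small strata at the clinic that recruits fewer patients.

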### Study Population

Partially and fully edentulous individuals reporting to the centers for routine dental care will be recruited for the study with their consent. Patients belonging to any gender, with/without prosthetic rehabilitation, and with/without any complaint of TMD with varied edentulous span will be included in the study.

### Clinical Definition

Patients presenting with pain in the jaw or temple area, pain or stiffness in the jaw, or pain on functional movements of the jaw (International Classification of Diseases, Tenth Revision, Clinical Modification Code M26.60). These symptoms are evaluated by the TMD screening questionnaire. Individuals giving a positive to any of the 3 screening questions in relation to the Diagnostic Criteria for Temporomandibular Disorders (DC/TMD) will be recruited to the study. The TMD pain screener has showed high sensitivity and specificity for detecting TMD pain [21].

### Eligibility Criteria

#### Inclusion Criteria

The following inclusion criteria will be used:

Individuals within an age limit of 20-80 yearsIndividuals completely or partially edentulous for a minimum period of 0-10 yearsCompletely or partially nonrehabilitated edentulous individualsPatients who show signs and symptoms of myalgia of facial musclesIndividuals who understand the importance of prosthetic rehabilitation and oral splints for TMDsIndividuals who are willing to report at the required intervals for evaluation

#### Exclusion Criteria

The participant may not enter the trial if *any* of the following apply:

TMD associated with macrotrauma of the headTMD associated with inflammatory/infectious/congenital disorders of the temporomandibular jointIndividuals with Class II, Class III, or transverse malocclusionIndividuals who refuse dental treatmentIndividuals with skeletal or dental developmental abnormalities and serious chronic medical conditionsAny other significant disease or disorder that, in the opinion of the investigator, may either put the participants at risk because of participation in the trial or may influence the result of the trial or the participant’s ability to participate in the trial

### Patient Selection

Partially and fully edentulous individuals reporting to the centers will be recruited for the study with their consent. Patients belonging to any gender, with/without prosthetic rehabilitation, and with/without any complaint of TMD with varied edentulous span will be included in the study. After obtaining an informed consent, these patients will be screened using the DC/TMD screener questionnaire. The patients who are screened positive and satisfy the inclusion/exclusion criteria will be recruited to the study. They will undergo detailed oral examination and the TMD examination using the DC/TMD Axis I and Axis II questionnaire. The electromyography (EMG) reading of these patients will also be recorded. These patients will be allocated to the specific arms of the study based on their dentulous state.

### Interventions

The participants will be grouped into 3 interventional and 3 control groups based on their state of edentulism (Figure 1; higher-resolution version in Multimedia Appendix 1). The interventional groups are:

Partially edentulous arch—Kennedy Class I and Class II: Kennedy Class I describes a patient who has edentulous areas bilaterally, posterior to the remaining natural teeth. Kennedy Class II describes a patient who has a one-sided edentulous area, posterior to the remaining natural teeth. The participants of this group will receive mouth preparation, prosthetic rehabilitation with removable partial denture, and comprehensive counseling (n=50).Partially edentulous arch—Kennedy Class III and Class IV: In Class III the edentulous area has teeth located both anteriorly and posteriorly to it. In Class IV, there will be a single but bilateral (crossing the midline) edentulous area located to the anterior of the remaining natural teeth. The participants of this group will receive mouth preparation and prosthetic rehabilitation with removable partial denture followed by management with stabilization splint and comprehensive counseling (n=50).Completely edentulous arches: The participants of this group will receive prosthetic rehabilitation with removable complete denture and comprehensive counseling (n=50).

Each of the 3 mentioned interventional groups will have their corresponding control groups with 50 participants in each control group. The participants in all the 3 control groups will receive symptomatic treatment and comprehensive counseling.

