#### Secondary Objective

The secondary objective is to determine the effect of the span of edentulism, the number of quadrants involved, pathological migration, the type of Kennedy classification, and the prosthetic status on temporomandibular joint dysfunction signs and symptoms.

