### Statistical Methods

The effectiveness of pain reduction within each arm and between each group will be analyzed using analysis of variance. The details of the analysis are explained in Table 3.

**Table 3 table3:** List of proposed analysis for trial results.^a^

Variable/outcome			Hypothesis		Outcome measure		Methods of analysis
Effectiveness of reduction of pain: within each arm			Intervention improved outcome from baseline to 12 months		Per person reduction of VAS^b^ score and GCPS^c^ (proportion or mean)		Chi-square methods or ANOVA^d^
Effectiveness of reduction of pain: between group 1, group 2, and group 3			Intervention improved outcome from baseline to 12 months		Per person reduction of VAS score and GCPS (proportion or mean)		Chi-square methods or ANOVA

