**Subgroup analysis**							
	Effectiveness of reduction of pain: between group 1, group 2, and group 3	Intervention improved outcome from baseline to 12 months		Per person reduction of VAS score and GCPS (proportion or mean)		Regression methods with appropriate interaction term	
	Between posterior teeth rehabilitation vs anterior teeth rehabilitation	Number of teeth affects effectiveness of outcome		Per person reduction of VAS score and GCPS (proportion or mean)		Chi-square methods	
	Upper vs lower teeth	Position of edentulism affects the effectiveness outcome		Per person reduction of VAS score and GCPS (proportion or mean)		Chi-square methods	
	Duration of edentulism	Duration of edentulism affects pain outcome		Per person reduction of VAS score and GCPS (proportion or mean)		Chi-square methods	
	Number of quadrants	Number of quadrants affects the effectiveness outcome		Per person reduction of VAS score and GCPS (proportion or mean)		Chi-square methods	

^a^In all analyses, results will be expressed as coefficient, SEs, corresponding 95%, and associated *P* values. Goodness of fit will be assessed by examining the residuals for model assumptions and chi-square tests for goodness of fit.

^b^VAS: visual analog scale.

^c^GCPS: Graded Chronic Pain Scale.

^d^ANOVA: analysis of variance.

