### Strengths and Limitations of This Study

This study has the following strengths and limitations:

The study design (RCT) will provide evidence of prosthetic rehabilitation on the TMD.Patients with TMD are grouped based on their edentulous state as completely or partially edentulous, and partially edentulous patients are classified further based on the Kennedy classification. This ensures that the effect of different types of edentulism on TMD are assessed.EMG reading for recording the muscle activity is an additional quantitative outcome evaluation used to assess and evaluate the TMD.As the study has a follow-up period of 3 months after the intervention, we expect some amount of attrition.

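### In Table 3 Kennedy type enters only through groups 1, 2 and 3, and between groups 1 and 2 it cannot be separated from the splint

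*Protocol article*

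**What the plan says.** The Secondary Objective asks for the effect of several features of edentulism, including "the type of Kennedy classification, and the prosthetic status on temporomandibular joint dysfunction signs and symptoms".

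Under Interventions the four Kennedy classes are merged into two groups whose treatment differs:

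- Group 1, "Kennedy Class I and Class II": "mouth preparation, prosthetic rehabilitation with removable partial denture, and comprehensive counseling (n=50" per the listing, closing bracket omitted here.
- Group 2, Classes III and IV: mouth preparation and "prosthetic rehabilitation with removable partial denture followed by management with stabilization splint and comprehensive counseling (n=50", again without the closing bracket.
- Controls: "The participants in all the 3 control groups will receive symptomatic treatment and comprehensive counseling".

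Table 3 under Statistical Methods uses the groups twice. One row is "Effectiveness of reduction of pain: between group 1, group 2, and group 3", by chi-square or ANOVA. The subgroup section repeats the same comparison with "Regression methods with appropriate interaction term". The other subgroup rows are posterior v anterior teeth, upper v lower teeth, duration of edentulism and number of quadrants. None is defined by Kennedy class.

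Strengths and Limitations says of grouping patients by edentulous state and Kennedy classification: "This ensures that the effect of different types of edentulism on TMD are assessed".

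**The concern.** Among partially edentulous patients in the intervention arms, knowing the Kennedy pair is the same as knowing whether a splint was given. Any group 1 v group 2 difference there can come from the pattern of tooth loss, from the splint, or from both, and no analysis of those two arms can divide it.

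The stake is interpretation. With Kennedy type a named objective and the strengths section saying that the grouping secures its assessment, a reader of the results would naturally take the group comparison as the answer. A splint effect could then be reported as a Kennedy effect, or a real Kennedy effect could be hidden by a splint effect in the opposite direction. The randomised comparison of intervention with control inside each group is not affected.

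**Working it through.** **Plan's own figure.** The article gives no sample size for a Kennedy comparison. Its only calculation, under Sample Size, is 22 per group for EMG (80% power, alpha .05, effect size 0.77). This reproduces as a one-sided t-test (21.6, rounded up to 22) but not two-sided (27.5, rounded up to 28). Nothing below depends on it.

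**Inputs.** 50 per arm in each group (Interventions; Table 2) and 1:1 allocation within group (Sequence Generation). Outcomes are in SD units and tests are two-sided at 0.05. Numbers per single Kennedy class are not fixed, since Table 2 sets quotas only for jaw and sex. The class splits and splint effects below are therefore assumptions.

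**Step 1: what the two rows estimate.** Let K be the effect of Classes III+IV relative to I+II on the outcome, M the change in the denture's effect between the pairs, and s the splint effect.

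- Intervention arms, group 2 minus group 1: K + M + s.
- Control arms, group 2 minus group 1: K.
- Group-by-arm interaction: (K + M + s) − K = M + s.

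The interaction removes K, the quantity in the objective, and keeps s. If the ANOVA row pools both arms, the splint contributes s × 50/100 = s/2, so it is diluted but still present.

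**Step 2: how often a splint effect alone would look like a Kennedy effect** (K = M = 0). Probability = Φ(s/SE − 1.96).

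- Intervention arms: SE = √(1/50 + 1/50) = 0.20.
- Interaction: SE = √(4/50) = 0.283.

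| Assumed s (SD) | Intervention arms | Interaction |
|---|---|---|
| 0.2 | 0.17 | 0.11 |
| 0.3 | 0.32 | 0.18 |
| 0.5 | 0.71 | 0.42 |
| 0.77 | 0.97 | 0.78 |

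**Step 3: the nearest other rows.** Number of quadrants overlaps with I v II (bilateral against one-sided). Posterior v anterior overlaps with III v IV. Neither is a Kennedy contrast, and neither is stated to be made within a group. If pooled over groups, both also carry the splint.

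**Step 4: comparisons free of the splint, and their precision.** Half-width = 1.96 × √(1/n₁ + 1/n₂).

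- I+II v III+IV among controls, 50 v 50: 1.96 × 0.20 = 0.39 SD.
- I+II v III+IV at baseline, both arms, 100 v 100: 1.96 × √(2/100) = 0.28 SD.
- I v II within group 1, or III v IV within group 2, adjusted for arm: 0.39 SD at 50 v 50; 1.96 × √(1/20 + 1/80) = 0.49 SD at 20 v 80. Within each arm both classes have the same assigned splint status.
- Class-by-arm term within one group: SE = √(2/25 + 2/25) = 0.40, half-width 0.78 SD; at 10 v 40 per arm, SE = √(2/10 + 2/40) = 0.50, half-width 0.98 SD.

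**The case against.** Four points on the other side deserve weight.

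1. *The design is not empty on Kennedy type.* This stands. The control arms have the same assigned treatment, and DC/TMD and EMG are recorded at baseline. A reader might infer that the trial cannot answer its Kennedy objective at all. The document does not support that: the data allow a splint-free comparison that Table 3 does not list.
2. *Single-class rows may be in the analysis plan.* This also stands. A reader might treat the lack of I v II and III v IV rows as a defect in itself, but a condensed article may leave such exploratory rows to a document not shown. The point rests on what the article does fix: an objective, a group comparison tied to the splint, and a claim that the grouping delivers the answer.
3. *The objective concerns signs and symptoms, not modification of the treatment effect.* This is correct. A reader might take the class-by-arm term as the key quantity, or as the only one free of the splint. It is neither. The main quantity is the class difference, whose half-width is half as large.
4. *The strengths claim is broader than Kennedy type.* True. It also covers complete v partial edentulism, and neither group 1 nor group 3 gets a splint. Only its Kennedy part is undermined.

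None of these separates the splint from the Kennedy pair in the two group rows of Table 3.

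**Conclusion.** The point holds in a limited form. As Table 3 stands, Kennedy type is analysed only through groups 1, 2 and 3. Between groups 1 and 2 it coincides completely with the splint in the intervention arms, and the interaction row does not remove the splint. This follows from the treatment definitions and needs no numerical assumption beyond reading the control treatment, which names no splint, as splint-free.

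The size depends on the unknown splint effect. For assumed effects of 0.2 to 0.77 SD with no Kennedy effect, a spurious Kennedy difference would appear with probability 0.17 to 0.97 in the intervention arms and 0.11 to 0.78 through the interaction.

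A secondary objective is affected and the primary one is not. The matter should be corrected, but it does not threaten the trial.

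**What to change.** Keep the groups, treatments and sample size.

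1. State beside Table 3 that group 1 v group 2 in the intervention arms, and the group-by-arm interaction, are not read as Kennedy effects. Limit the sentence in Strengths and Limitations to match.
2. Add comparisons of signs and symptoms, labelled non-randomised and exploratory, with 95% intervals:
   - (a) I+II v III+IV at baseline and among the control arms;
   - (b) I v II within group 1 and III v IV within group 2, adjusted for arm, using the class recorded at the baseline oral examination.
3. A class-by-arm term may be added if its low precision (half-width about 0.78 to 0.98 SD) is stated.

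The cost is one recorded field, since the patient has to be classified anyway to be placed in a group, and a few analysis rows. The downsides are wide intervals, class numbers that are not fixed and may be uneven, and the need for a rule for patients whose two arches differ in class. These comparisons are free of the splint only. They still compare different kinds of patient and should be reported that way.
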